### Outcome measures

The primary outcome will be success after two years follow-up. Success is defined as the absence of POP beyond the hymen in any compartment (POP-Q, gynaecological examination), the absence of bulge symptoms (absence of bulge symptoms is defined as a negative response to the question, “Do you see or feel a bulge in the vaginal area” (UDI domain genital prolapse score: 0)), and absence of reoperation or pessary therapy for POP [27].

Secondary outcomes of the study will be clinical parameters (surgery time, hospitalisation time), surgery related morbidity/complications (including menstrual problems, hematometra, any problems with uterine access such as diagnostic cervical or endometrial sampling or IUD insertion), pain perception, further treatments for POP or urinary incontinence, anatomy in all compartments using POPQ [28], general quality of life, disease specific quality of life regarding symptoms and impact of symptoms, sexual function, and costs.

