### Data collection

All women will undergo gynaecological examination including POP-Q which must be done in 45 degrees supine position. All measurements performed during pre-operative and follow-up outpatients visits, as well as the operation report, will be systematically recorded in an electronic Case Report Form in Castor. All data will be kept anonymous where possible. All participants will be assigned an identification code based on number of the hospital and number of inclusion. A list linking the code to the subject will be kept safe by the local investigators. Personal data will be stored for a maximum of 15 years in participating centres.After randomization patients will be sent an e-mail with a link to the pre-operative questionnaires in Castor. If the subject prefers paper questionnaires, written informed consent is needed to get insight in the postal address of the subject. Both groups will fill in the same questionnaires. The pre-operative questionnaire consists of questions on baseline characteristics, and standardized, validated questionnaires about quality of life (EQ5D-5 L: EuroQol-5D-5 L) [30], disease specific quality of life regarding symptoms (Pelvic Floor Disability Index-20) and the impact of those symptoms (Pelvic Floor Impact Questionnaire-7) [31], sexual function (Pelvic organ prolapse Incontinence Sexual Questionnaire-IR) [32], and the validated cost utility questionnaires of the institute for Medical Technology Assessment (iMTA) (PCQ: Productivity Cost questionnaire and MCQ: Medical Consumption Questionnaire) [33]. After surgery, the patients will visit the hospital at 6 weeks, 12 months and 24 months (see Table 1). During the follow-up specific history taking and gynaecological examination including POP-Q will be done. The POP-Q at 12 and 24 months will be performed by another researcher than the operating gynaecologist. Reimbursement of travel expenses is available to minimize no shows. At 6 months, 12 months and 24 months patients will receive abovementioned questionnaires and an additional disease specific questionnaire (Patient Global Impression of Improvement). At 12 weeks and 9 months patients receive the PCQ, MCQ and EQ5D-5 L; these extra moments are incorporated to prevent recall bias. Reminders will be sent after two weeks in case of non-completion of questionnaires. The duration of the follow-up period is set at 2 years because the majority of recurrences after POP surgery will occur in these first two years [34, 35]. Women will be asked for permission to ask them to participate in a longer follow-up study in case this seems valuable after the two year analysis.

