
**Table 1 Tab1:** Schematic overview of follow-up

Measurement	Follow-up moment						
	Pre-op	6 wks	12 wks	6 months	9 months	12 months	24 months
Outpatient visit including POP-Q		x				x	x
Baseline characteristics	x						
EQ5D-5 L	x		x	x	x	x	x
PDFI-20, PGI-I, PFIQ-7, PISQ-IR	x^a^			x		x	x
PCQ and MCQ			x	x	x	x	x

^a^without PGI-I

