## Statistical analysis

### Data analysis

Regarding the primary outcome, the null hypothesis entails that the success rate of SSH is inferior by a margin of 9% compared to MM. If the lower limit of the 95% confidence interval does not exceed the margin of − 9%, the null hypothesis is rejected, and we will consider SSH to be non-inferior to MM. The statistical analysis will be performed both by the intention to treat (ITT) and per protocol (PP) principle. This means that non-inferiority has to be demonstrated in both the ITT and PP analysis to declare non-inferiority of SSH compared to MM. The treatment effect will be expressed as relative risk with a 95% confidence interval.

For other (secondary) outcomes, summaries of continuous data will be presented as mean ± standard deviation or median and (interquartile) range depending on their distribution. Categorical data will be presented as frequencies. When appropriate, differences between groups will be analysed using the Student’s t test or Mann-Whitney test for continuous data. Comparisons with categorical data will be analyzed using the Chi-square test of the Fisher’s exact test.

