## Discussion

This is a protocol for a randomized clinical trial comparing SSH with MM. To our knowledge this will be the first large randomized study with mid-term follow-up that will compare these two uterus sparing operative techniques. The study will provide knowledge that can lead the way in the best individual treatment in women with POP, can be used to supplement the current guidelines and may show the need for de-implementation of one of the procedures. The study will reveal whether the existing PPV is unwanted or not significant in terms of effectiveness and costs. In case non-inferiority is found, the secondary outcomes might determine the preferred uterus preserving technique.

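### Continuous secondary outcomes that have a pre-operative value are to be compared by unadjusted two-sample tests: valid, but less precise than a baseline-adjusted comparison of data already collected

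*Protocol article*

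**What the plan says.** The Data analysis section gives one between-group method for continuous secondary outcomes. The sentence opens "When appropriate, differences between groups will be analysed using the" and goes on to Student's "t test or Mann-Whitney test for continuous data". It names no baseline covariate, change score or repeated-measures term.

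The outcomes concerned are listed under Outcome measures. They include POP-Q anatomy and "general quality of life, disease specific quality of life regarding symptoms and impact of symptoms, sexual function, and costs".

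The Data collection section provides the baseline: "The pre-operative questionnaire consists of questions on baseline characteristics, and standardized, validated questionnaires about quality of life", followed by disease-specific quality of life and sexual function. On follow-up it says "At 6 months, 12 months and 24 months patients will receive abovementioned questionnaires". Table 1 adds EQ5D-5L at 12 weeks and 9 months. On the timing of the baseline it says "After randomization patients will be sent an e-mail with a link to the pre-operative questionnaires in Castor".

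The Discussion gives these outcomes a role in the recommendation: "In case non-inferiority is found, the secondary outcomes might determine the preferred uterus preserving technique".

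**The concern.** A woman's score two years after surgery usually depends in part on her score before it. A two-sample test on the follow-up scores leaves that predictable part in the error term, whereas adjusting for the baseline removes it. The article collects the baseline and then names a method that does not use it.

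The sample size was set for the primary outcome alone, so the precision of the quality-of-life, sexual-function and anatomy comparisons is whatever that number yields. If non-inferiority is shown, these comparisons may help to decide which operation is preferred. Wider intervals than necessary would make that choice less well informed.

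**Working it through.** **Which outcomes have a baseline.** By Data collection and Table 1:

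- EQ5D-5L: pre-operative, then 12 weeks and 6, 9, 12 and 24 months.
- PFDI-20, PFIQ-7, PISQ-IR: pre-operative, then 6, 12 and 24 months.
- POP-Q points: 6 weeks, 12 and 24 months. The Table 1 row "Outpatient visit including POP-Q" has no pre-operative mark. Eligibility depends on POP-Q point D, however, and Data collection refers to measurements at pre-operative visits, so a pre-operative POP-Q is implied.
- PGI-I, surgery time, hospital stay: no baseline. The point does not apply to them.

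**Is baseline used elsewhere?** Baseline characteristics enter the subgroup and prognostic-marker analyses (Other study parameters). The only regression model named for a between-arm comparison of a continuous outcome is the gamma model for costs (Economic evaluation). Neither covers the outcomes above.

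**The plan's own figure.** The article gives no power figure for secondary outcomes. Its primary sample size supplies the number per arm. With 89% success in both arms, a margin of 0.09, one-sided alpha 0.025 and 80% power:

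n = (1.960 + 0.842)² × 2 × 0.89 × 0.11 / 0.09² = 190 per arm

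This is close to the stated 193. The total follows as 386 × 1.10 = 424.6, against the stated 424. I use 193 per arm as the number analysed.

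**Detectable difference, unadjusted.** At two-sided 5% and 80% power:

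(1.960 + 0.842) × √(2/193) = 0.285 SD

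**Effect of adjustment.** Let r be the correlation between baseline and follow-up. The document does not give it; 0.2 to 0.6 is an assumption. Relative to the unadjusted comparison:

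- variance ratio = 1 − r²
- unadjusted sample size of equal precision = 193 / (1 − r²)
- power at 0.285 SD = Φ(2.802/√(1 − r²) − 1.960)

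| r | Variance ratio | Reduction | Equivalent n per arm | Power |
|---|---|---|---|---|
| unadjusted | 1.00 | – | 193 | 80% |
| 0.2 | 0.96 | 4% | 201 | 82% |
| 0.3 | 0.91 | 9% | 212 | 84% |
| 0.4 | 0.84 | 16% | 230 | 86% |
| 0.5 | 0.75 | 25% | 257 | 90% |
| 0.6 | 0.64 | 36% | 302 | 94% |

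**Simulation check** (3,000 trials per setting, 193 per arm, normal scores). At 0.285 SD the t test had 81% and 80% power for r = 0.3 and 0.5, and ANCOVA had 84% and 90%. With no true difference and r = 0.3, 0.5 and 0.7, rejection rates were 4.7% to 5.6% for the t test and 4.8% to 5.3% for ANCOVA. Both methods are valid.

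**If the t test were run on change scores.** The article does not say that it would be. The variance ratio is then 2(1 − r): 1.6 at r = 0.2, 1.0 at 0.5 and 0.8 at 0.6. This is worse than ignoring the baseline when r is below 0.5. It is also worse than ANCOVA at every r below 1, because (1 − r²) / [2(1 − r)] = (1 + r)/2, which is less than 1.

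**The case against.** The strongest reply is that nothing here is an error. A two-sample test on randomised arms keeps its type I error, as the simulation shows. A reader might infer that chance baseline imbalance biases the comparison. It does not: the standard error of the unadjusted test already allows for such imbalance, and the variance it contributes is the r² share that adjustment would remove. Nor does anything here reach the primary outcome. These objections stand and limit the point to efficiency.

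A reader might also infer that the protocol commits itself to throwing the baseline away. The qualifier at the start of the sentence leaves some room, the text does not say whether raw or change scores would be tested, and an unseen analysis plan may say more. That softens the point without removing it, since the only method named is an unadjusted one and no alternative is offered.

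The size of the gain depends wholly on an assumed correlation; at 0.2 it is small. Several outcomes that could sway the preference, such as surgery time, complications and further treatments, have no baseline. The Discussion says only that secondary outcomes might determine the choice.

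The most serious objection concerns the remedy. The questionnaire baseline is collected after randomisation in a trial that cannot be blinded. If knowing the allocation shifts baseline answers by d SD between arms, adjustment moves the estimate by about r × d. For illustration, r = 0.5 and d = 0.1 give 0.05 SD. The unadjusted comparison does not have this weakness. In addition, a woman without a baseline would drop out of a baseline-adjusted model altogether, and skewed scores need more than a plain linear model. All of this stands and shapes the fix.

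**Conclusion.** The point holds as one of precision. For EQ5D-5L, PFDI-20, PFIQ-7, PISQ-IR and POP-Q points, the named tests are valid but less precise than a baseline-adjusted comparison. With r from 0.2 to 0.6, 193 women analysed per arm and roughly normal scores, the variance of the treatment difference is 4% to 36% lower after adjustment. Power at 0.285 SD is then 82% to 94%, compared with 80% unadjusted. That the stated method omits the baseline can be read from the text; how much this costs cannot, because the correlation is assumed. This is a worthwhile improvement to secondary analyses. It does not correct a faulty test, and the primary non-inferiority conclusion is unaffected.

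**What to change.** - **Model.** For the outcomes with a pre-operative value, replace the two-sample test as the main analysis. Use either ANCOVA at 24 months adjusted for baseline, or a mixed model over all scheduled visits (including 12 weeks and 9 months for EQ5D-5L; 6 weeks, 12 and 24 months for POP-Q) with baseline, treatment, time and treatment-by-time. Report adjusted mean differences with 95% confidence intervals.
- **Missing baseline.** Impute it so that these women stay in the analysis.
- **Skewed scores.** State a transformation, a bootstrap interval or a rank-based check.
- **Timing of the baseline.** Where possible, have the questionnaires completed before the allocation is disclosed, and record the completion date. Keep the unadjusted comparison as a sensitivity analysis.
- **Outcomes without a baseline.** Keep the t or Mann-Whitney test for surgery time, hospital stay and PGI-I.

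The cost is a little extra analysis work, which the stated software (SPSS) can handle, and the recording of a completion date. No further outcome data are needed. The price is some reliance on a questionnaire baseline collected after randomisation, which the sensitivity analysis makes visible.

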### Other study parameters

Subgroup analyses are planned to investigate the effects of the POP surgery with MM versus SSH in the following pre-specified subgroups: age, menopausal status, sexual activity, POP-Q stage, cervical elongation, concomitant vaginal repair and symptoms.

A prognostic marker analysis will be performed to assess which baseline characteristics of the women have prognostic value and/or can be used as treatment selection markers. Missing covariates will be imputed as appropriate (with solid logical strategy). We will use multiple imputation based on other baseline variables that are associated with higher or lower values of the variable that is imputed. We will do sensitivity analyses to evaluate the difference between imputed and non-imputed variables. All analyses will be performed with IBM SPSS Statistics (version 25, Armonk, New York, United States).

### Economic evaluation

The economic evaluation will be performed along-side the clinical trial, which will compare the cost-effectiveness up to 12 months after surgery from a societal perspective. The design of the economic evaluation follows the principles of a cost-utility analysis and adheres to the Dutch guideline for performing economic evaluations in health care [36]. Costs and effects will be measured on a per patient basis. The cost analysis exists of two main parts. On patient level, the costs made within healthcare, costs made by patients/family and costs in other sectors than healthcare will be included. Second, per item of health care consumption standard cost-prices will be determined using the guideline for performing economic evaluations [36]. If standardized prices are not available, full cost prices will be determined via activity-based costing. Productivity losses for patients will be assessed using the iMTA PCQ. The friction-cost method will be applied and in addition, travel time to the hospital and related costs will be considered. It is anticipated that SSH is as effective but significantly cheaper (less operating time) than MM in this target population. If the results confirm this, a cost-minimization analysis will be the method of analysis. Cost will be analysed using a generalized linear model approach with a gamma distribution using a log link to account for possible skewness of the cost data. The effect analysis measures, on previous mentioned follow-up moments, the clinical trial Health Related Quality of Life using de EQ5D-5 L.

Additionally, a budget impact analysis will be performed for consequences of implementation of SSH substituting for MM in the Dutch health care system in the short-to-medium term from the budget holders perspective [37]. The economic analyses will be presented as a separate study.

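### The economic evaluation would move from cost-utility to cost-minimisation depending on results, with equal effectiveness undefined, and its cost-effectiveness comparison stops a year before the primary outcome

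*Protocol article*

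**What the plan says.** The Economic evaluation section of the protocol article makes four statements that bear on this point.

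- **Design:** "The design of the economic evaluation follows the principles of a cost-utility analysis". The effect measure named there is "the clinical trial Health Related Quality of Life using de EQ5D-5 L".
- **Horizon:** the evaluation will "compare the cost-effectiveness up to 12 months after surgery from a societal perspective".
- **Expectation:** "It is anticipated that SSH is as effective but significantly cheaper (less operating time) than MM in this target population".
- **Rule:** "If the results confirm this, a cost-minimization analysis will be the method of analysis".

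Other sections set the clinical timing. Under Outcome measures, the primary outcome is success at two years, and reoperation or pessary therapy counts as failure. Data collection justifies two years on the ground that "the majority of recurrences after POP surgery will occur in these first two years". The same section states "At 6 months, 12 months and 24 months patients will receive abovementioned questionnaires", and Table 1 schedules EQ5D-5L, PCQ and MCQ at 24 months as well as at 12 weeks and 6, 9 and 12 months. The Implementability section says the trial should lead to adoption of the more cost-effective uterus-sparing technique.

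**The concern.** A cost-utility analysis estimates incremental cost and incremental QALYs together and carries the uncertainty in both. Cost-minimisation keeps only the cost side and treats the effect difference as known to be zero. Here the change of method depends on the trial's own results, and the first half of the condition, equal effectiveness, is tied neither to EQ5D-5L nor to the clinical composite, and has no threshold.

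The only formal effectiveness test in the article is non-inferiority of the 24-month composite with a 9-point margin. If that is the intended trigger, a finding that SSH is not much worse on one outcome would be used as if it showed no difference on another. The second half of the condition, that SSH is cheaper, means the switch happens only when SSH already saves money. That is where any small loss of health would have to be weighed against the saving.

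The horizon adds a mismatch. Retreatment costs and utility losses in the second year fall outside the cost-effectiveness comparison, although the trial follows women through that year and collects the relevant questionnaires at its end. The economic result may help decide which operation is kept, because the Discussion says secondary outcomes may settle the preferred technique once non-inferiority is found.

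**Working it through.** The economic section gives no figure of its own. The check therefore asks how large an effect difference could be dropped if equal effectiveness is read as the non-inferiority finding. That reading is an assumption.

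**Inputs** (Sample size calculation and Data analysis): success 89% in both arms; margin 9 points; one-sided α 0.025; power 80%; 193 evaluable per group; non-inferiority is declared when the lower 95% confidence limit for SSH minus MM lies above −9 points.

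**1. The plan's figure.** With unpooled variance,

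n = (1.960 + 0.842)² × 2 × 0.89 × 0.11 / 0.09² = 189.7, so 190 per group against 193 stated (within 3%). The exact binomial power of the confidence-interval rule at 193 per group is 80.9%. The design figure reproduces.

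**2. Largest observed deficit that still passes.** With MM at 0.89 and SSH at 0.89 − d, the rule requires

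d + 1.96 × √{[0.89 × 0.11 + (0.89 − d)(0.11 + d)] / 193} < 0.09.

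At d = 0.0247 the standard error is 0.0333, the half-width is 0.0653, and the sum is 0.090. The limit is therefore about 2.5 points (2.7 points with 212 per group). In whole patients:

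| MM successes of 193 | SSH successes of 193 | Observed deficit (points) | Lower 95% limit (points) | Non-inferior |
|---|---|---|---|---|
| 172 | 168 | 2.07 | −8.53 | yes |
| 172 | 167 | 2.59 | −9.11 | no |

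So an observed deficit of about 2 to 2.5 points is the most that could be set to zero on this reading.

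**3. Chance that a true deficit passes.** Exact binomial calculation, 193 per group, MM at 89%:

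| True SSH deficit (points) | Probability of declaring non-inferiority |
|---|---|
| 0 | 81% |
| 2 | 57% |
| 3 | 44% |
| 4 | 32% |
| 5 | 22% |
| 6 | 14% |
| 9 | 2.7% |

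These figures are for a single analysis. The plan requires both the ITT and the PP analysis to succeed, which cannot raise the chance in either one. The switch also needs SSH to be cheaper, so its probability is no higher than the probability of passing.

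**4. Timing, side by side.**

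| Item | Time point |
|---|---|
| Cost-effectiveness comparison | to 12 months |
| Primary outcome, including reoperation and pessary therapy | 24 months |
| EQ5D-5L, PCQ, MCQ (Table 1) | 12 weeks; 6, 9, 12 and 24 months |

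If the effectiveness judgement comes from the composite, a 24-month effect finding would be paired with 12-month costs. The article gives no split of recurrences between years one and two, so the size of the omission cannot be computed.

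**The case against.** **The 9-point reading.** A reader might infer that up to 9 points of lost success would be ignored: 20% failures against 11%, scaled to the roughly 3000 MM operations a year given in the Background. The documents do not support this. Nine points is what the confidence interval must exclude, and a true deficit of that size passes only about 3% of the time. Scaling to all MM operations also assumes complete substitution and that all those women resemble the trial population. Nor does the article say that equal effectiveness means non-inferiority; it names EQ5D-5L as the effect measure in the same section.

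**Bias towards SSH.** A reader might also infer that the method must favour the shorter operation. This is not shown. Setting the effect difference to zero would equally erase an SSH advantage, and leaving out year two helps whichever arm has more late recurrences. No passage says which that is. Cost-minimisation also still counts retreatment costs within the horizon.

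**Pre-specification.** The switch was published in advance as a conditional rule, so it is not post hoc selection. That is true, but the condition is undefined, and the rule still discards effect uncertainty when it operates.

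**The horizon.** Twelve months has a visible rationale: the 12-week and 9-month questionnaires were added against recall bias, whereas months 12 to 24 have one collection. This supports keeping 12 months as the main horizon. It does not support leaving the second year out altogether. The budget impact analysis does not fill the gap, because it takes the budget holder's perspective and is not a cost-effectiveness comparison.

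**The separate economic study.** Methods for handling uncertainty may be set out in a fuller plan, and their absence here is no finding. The switch and the horizon, however, are stated in this article.

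**Conclusion.** The point holds as a flaw in the economic analysis; it does not touch the primary clinical conclusion. Followed as written, the rule replaces a declared cost-utility analysis with one that drops the EQ5D-5L difference and its joint uncertainty with cost, on a condition whose effectiveness half is undefined.

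The size rests on two assumptions: that equal effectiveness means the trial's non-inferiority result, and that 193 per group are evaluable with MM success at 89%. On those terms the loss that could be disregarded is modest in observed data, about 2 to 2.5 points, but it is compatible with true deficits of 3 to 5 points, which would pass 44% to 22% of the time. What such deficits mean in QALYs cannot be derived from the article.

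The horizon mismatch needs neither assumption. Second-year costs and utilities are outside the stated comparison although data are scheduled. The direction and size of any resulting bias are unknown. The change is worth making because the results are meant to guide which technique is implemented.

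**What to change.** 1. Delete the cost-minimisation switch. Run the declared cost-utility analysis whatever the clinical result, reporting incremental costs and QALYs with their joint uncertainty.
2. Keep 12 months as the stated horizon and pre-specify a second analysis to 24 months, using the EQ5D-5L, PCQ and MCQ already scheduled then and the reoperation and pessary data recorded for the primary outcome.

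No new data collection is needed. The cost is additional analysis work. Months 12 to 24 would rest on a single questionnaire with longer recall than in year one, and this should be reported as a limitation of the second analysis.
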